### Eligibility criteria

Eligibility criteria for the inclusion and/or exclusion of candidate participants are listed in Table 2. After information sessions at the research sites, eligibility criteria are preliminarily assessed for interested candidate participants. After the assessment, informed consent is requested to proceed with formal recruitment, which will start exclusively when informed consent is properly understood and signed by the participant. Informed consent will be obtained, from the participant or legal guardians of under 16 years old volunteers, by the study nurses who will enrol formally the participants just after signature.

**Table 2 Tab2:**
[figure not shown]
Eligibility criteria for the selection of the participants (pregnant women and later on children). The eligibility criteria are preliminary assessed after information sessions at the research sites. After assessment informed consent is requested to proceed with formal recruitment upon its reception

### Outcomes

The primary endpoints of the study are as follows:
The proportion of children showing stunted growth (height-for-age *z*-value < − 2) at 2 years of age to measure the impact of TBST on child developmentMaternal Hb at 24 months after delivery to measure the impact of TBST on maternal health

The secondary endpoints of the study are as follows:
Sensitivity and specificity of the POC-CCA test compared to a panel of reference standard tests (measured as part of the cross-sectional study at non-randomized sites)Women’s health-related quality of life, capacity to work and participate in economic activities and cost-effectiveness of the interventions

### Data collection plan

The baseline visit was conducted following informed consent and eligibility assessment. At enrolment, a unique identifier of 12 digits was assigned to each participant. The identifier is connected within the mother-child tandem and will be kept identical throughout the course of the study. Demographics and short medical history were obtained**.**

All sites have the same visit schedule. The sampling scheme is the same for the intervention and control sites; thus, the only difference between intervention and control sites is the TBST strategy at the intervention sites.

A POC-CCA-TBST is scheduled in the intervention arm at the following:
Recruitment (5th to 6th month of pregnancy) and 9 months after delivery for the pregnant women/mothersNine months of age for the children

A POC-CCA-TBST is scheduled in both arms at the following:
Twenty-four months of age of children for both mother and child

The visit schedule of freeBILy is integrated into the mother and child care scheme offered to all pregnant women at the CSBs in Madagascar. freeBILy includes 5 different visits (T0, T1, T2, T3, T4) according to the following scheme as summarized in Table 3.

**Table 3 Tab3:**
[figure not shown]
Scheme of scheduled visits. T0 mothers enrolment at 5^th^ or 6^th^ month of pregnancy pregnancy; T1 pre-delivery follow up at the 8^th^ month of pregnancy; T2 delivery follow up at birth and inclusion of children; T3 follow up 9 month after delivery; and, T4 final follow up 24 months after delivery

T0: mother’s enrolment during the 5th or 6th month of pregnancy. Haemoglobin is measured on-site using the Hemocue® system, and a urine sample is being collected (≥ 25 ml). In the TBST intervention arm, the POC-CCA to test for schistosomiasis infection is done on-site. Women who test positive are offered (40 mg/kg) PZQ treatment. Additional samples (Table 4) are being collected at the non-randomized sites for the cross-sectional sub-study to assess the sensitivity and specificity of the POC-CCA test against a panel of reference tests described in Table 4.T1: 1st follow-up, 8th month of pregnancy. Haemoglobin is measured on-site by means of the Hemocue® system.T2: 2nd follow-up, delivery and child enrolment. The case report form (CRF) is completed. The newborns are included, unless the mother decides to withdraw her/him from the study. Weight and height of the newborns are measured.T3: 3rd follow-up, 9 months after delivery/birth. Haemoglobin is measured for all women using the Hemocue® system. Height and weight are measured for all children. A urine sample is being collected (≥ 25 ml) from all mothers and children. In the TBST intervention arm, the POC-CCA to test for schistosomiasis infection is being performed on-site for the mother and child. To test-positive mothers, a 40 mg/kg dose of PZQ treatment is offered. Test-positive children are treated with 300 mg.T4: 4th follow-up, 24 months after delivery/birth. Haemoglobin is measured for all mothers on-site using the Hemocue® system. Height and weight are measured for all children. A urine sample is being collected (≥ 25 ml) from all the women and children. In both arms, the POC-CCA test for schistosomiasis infection is being performed on-site for the mothers and children. All positive women and children are offered 40 mg/kg and 300 mg PZQ treatment, respectively.

**Table 4 Tab4:**
[figure not shown]
Scheme of scheduled visits. At T0 blood and stool samples will be collected from 1000 women, urine samples from 5200 women. At T1 capillary blood will be collected from 5200 women. At T2 no biological samples will be collected. At T3 and T4 capillary blood will be collected from all the women attending the follow-up visit, urine will be collected from all the participants attending the follow-up visit. Considering the loss to follow up 4472 mothers and 4472 children are expected at T3 to remain in the study and 3900 women and 3900 children at 4. UCP-CF (Up-Converting Phosphor – Consecutive Flow) antibody assay will be performed on serum samples. Hb will be measured on capillary blood. UCP-LF-CAA (Up-Converting Phosphor – Lateral Flow) and POC-CCA will be performed on urine samples. PCR will be performed on urine, plasma and stool samples. Microscopy will be performed on stool samples

All the samples collected for further laboratory analysis at the two non-randomized centres are stored on-site at the required temperatures and delivered to the laboratories within 1 week. Tables 4 and 5 summarize the testing and the sampling schemes. The tests will be performed according to standardized protocols described in [11–15, 18–25].

**Table 5 Tab5:**
[figure not shown]
Testing scheme by randomization group. The UCP-LF antibody assay will be performed at the designated laboratory on all the samples collected at T0 from the women attending the visit at both intervention and control training centres. The maternal Hb will be measured at the CSB from all the women in all the sites attending T0, T1, T3 and T4 visits. The UCP-CF CAA and the UCP-LF CAA assays will be performed at the designated laboratory on all the samples collected at T0 from all the women in all the sites and at T3 from all the children in all the sites. The POC-CCA test will be performed for all the women attending the T0, T3 and T4 visits and for all the children attending T3 and T4 visits at the CSB belonging to the intervention group. The POC-CCA test will be also performed at the designated laboratory on all the samples collected at T0 from all the women in all the sites and at T3 from all the women and children in all the sites. PCR will be performed at the designated laboratory on all the samples collected at T0 from the women attending the visit at both intervention and control training centres. Microscopy will be performed at the designated laboratory on all the samples collected at T0 from the women attending the visit at the intervention training centre (one of the two non-randomised centres)

Information on women’s health-related quality of life is collected at T0, T1, T3 and T4 in a sub-sample of women enrolled at the non-randomized centres. Information on health system resources used for TBST is collected in all the facilities by means of a simple questionnaire administered to nurses involved in the intervention.

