**Fig. 3 Fig3:**
[figure not shown]
Design of the cross-sectional study. The two non-randomized CSBs Andina and Imerintsiatosika were selected as the intervention and non-intervention sites, respectively. At the 5th or 6th month of pregnancy (T0), women will be enrolled in the study and consent for their children will be asked. At T0, blood, urine and stool samples will be collected. At the end of the study, the sample will be analysed with the tests described in Table 3. At 8 months of pregnancy (T1) and 9 (T3) and 24 (T4) months after birth, urine samples will be collected. At delivery (T2), children will formally become part of the study

The units of randomization are the PHCC, called *Centres de Santé de Base* (CSB). There is a total of 23 CSBs in the Antananarivo and 49 CSBs in the Fianarantsoa study area. On the basis of the criteria listed in Table 1, 20 CSBs from the Antananarivo region (10 intervention and 10 control arms) and 20 CSBs from the Fianarantsoa region (10 intervention and 10 control arms) were selected. In addition to these 40 randomized CSBs, two non-randomized CSBs have been included in the trial: one is assigned to the intervention arm (Andina) and the other to the control arm (Imerintsiatosika). Objectives 1 and 2 are rolled out in the 40 randomized CSBs. Objectives 3 and 4 are rolled out in the two non-randomized CSB.

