### Intervention

In study centres of the intervention arm, the POC-CCA-TBST is being implemented among pregnant women between week 20 of pregnancy and delivery and at 9 months after delivery and among their babies at 9 months of age. The urine-based POC-CCA-test is done, and PZQ treatment is offered in case of a positive diagnosis. In the study centres of the control arm, no TBST is carried out, and in case of clinical suspicion of schistosome infection, the participants are referred to the local health system. At the 24 months’ time point, TBST is being applied in both arms.

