### Sample size and statistical analysis

The sample size was calculated in relation to the primary child outcome proportion showing stunted growth at 2 years of age, for which a larger sample size is assumed to be necessary than for the maternal outcome (Hb, 2 years after delivery).

The prevalence of stunting in Madagascar is estimated to be 40% of children under 2 years of age [26]. For our sample size estimate, it was conservatively assumed that:
Twenty per cent of all children at the age of 2 years are stunted (height-for-age *z*-score < − 2)The intervention can reduce the proportion of stunted children by 50% in infected individuals, i.e. to observe that 10% of all children at the age of 2 years are stunted in the intervention arm.

In order to estimate the appropriate number of infected individuals at 9 months of age, sample sizes with power values of 80% and 90% were subsequently calculated using the OpenEpi tool [27]. For a power of 80%, at least 394 infected individuals at 9 months of age would be required and for a power of 90% 526 individuals. The design effect was assumed to be 1.9 by which the initial sample size needs to be multiplied to account for the clustered design of the study. This leads to a sample size of 749 for 80% power and 1000 for 90% power.

With an annual loss to follow-up of 10% from a visit to visit and an infant mortality rate of 4%, 86% of all mother-infant tandems are expected to present for the 9-month visit. For the 2 years visit, a loss to follow-up of around 10% between 9 months and 2 years is assumed, so that around 0.86 × 0.9 = 77.4% of all mother-infant tandems are expected to present for the 2-year visit. To correct for loss to follow-up, we use the factor 1/0.774 = 1.3. Since our analyses only focus on women infected with schistosomiasis, the number of women to be recruited needs adjusting, considering that the expected prevalence of 0.25 results in an additional inflation factor of 4 leading to an inflation factor of 1.3 × 4 = 5.2.

We hence planned to enrol 4200 eligible pregnant women in the 40 randomized cluster of the trial ensuring a power between 80 and 90% and an additional 1000 participants for the cross-sectional sub-study in the non-randomized sites. Based on the 40 randomized clusters identified for this study, an average of 105 women per cluster is needed to be recruited per cluster.

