### Analysis for the secondary outcomes

To measure the sensitivity and specificity of the POC-CCA, the test results of the 1000 urines collected at the non-randomized sites at T0 will be compared to the results obtained from the reference panel (Table 5). Sensitivity of the POC-CCA is defined as the number of samples positive in the POC-CCA test divided by the total number of “true” positives (according to the results obtained from the combined panel of reference tests described in Table 5). Specificity of POC-CCA will be the number of sample negatives in the POC-CCA test divided by the total number of “true” negatives.

Additionally, women’s health-related quality of life scores will be compared between women in the intervention and in the control arms (Wilcoxon rank-sum test will be applied). A multivariate two-way fixed effects, regression model will be used to evaluate the effect of the intervention (while controlling for other factors) on women’s health-related quality of life scores. Finally, the costs of the intervention and health indicators will be used for the cost-effectiveness analysis. A decision tree model will be estimated and where the natural history of the disease will be represented by a Markov model. The model will be estimated by following standard approaches (i.e., deterministic and probabilistic analyses will be conducted). The association between women’s capacity to work and the intervention will also be estimated using the two-way fixed effects regression analysis, while controlling for observable time-varying factors.

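### The accuracy sub-study pools 1000 women from two sites against one reference panel, but Table 5 plans microscopy at only one of them, Table 4 does not agree, and the index reading is not named

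*Protocol article*

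**What the plan says.** All references are to the protocol article, Methods.

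- **Analysis.** Under Analysis for the secondary outcomes, "the test results of the 1000 urines collected at the non-randomized sites at T0 will be compared to the results obtained from the reference panel". True positives and negatives are set "according to the results obtained from the combined panel of reference tests described in Table 5". No split by site is mentioned.
- **Sites.** The section Sample size and statistical analysis plans "an additional 1000 participants for the cross-sectional sub-study in the non-randomized sites". There are two such sites, one assigned to each arm (Trial design and location).
- **Table 5 caption.** The antibody assay and PCR are run on enrolment (T0) samples from both training centres, and the CAA assays on T0 samples from women at all sites. Microscopy is run on samples "from the women attending the visit at the intervention training centre (one of the two non-randomised centres".
- **Table 4 caption.** "At T0 blood and stool samples will be collected from 1000 women", and microscopy is listed for stool with no restriction by site.
- **POC-CCA readings.** The on-site test at T0 belongs to the intervention arm (Data collection plan). The Intervention section adds: "In the study centres of the control arm, no TBST is carried out". The Table 5 caption also provides a laboratory POC-CCA on every T0 sample from all women at all sites.
- **Objective.** The third specific objective is the accuracy of the POC-CCA within routine maternal and child primary care.

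**The concern.** A composite reference standard gives one sensitivity and one specificity only if every woman is classified by the same set of tests. Under the Table 5 caption, one site has a test in its panel that the other lacks. Whether microscopy was done is then fully confounded with site. An infection that only microscopy would find could count as a true positive at one centre and a true negative at the other. The pooled figure would be a mixture that depends on how many women each site contributed.

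A second matter decides what is being estimated. On-site and laboratory readings of the same test answer different questions. The objective asks about routine care, but a reading common to all 1000 women exists only in the laboratory. The analysis text does not separate the two.

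Accuracy is a named secondary endpoint, and the Discussion intends the trial's findings to inform national guidelines.

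**Working it through.** **1. No plan figure to reproduce.** The article gives no target accuracy or precision behind the 1000. The count agrees with the total: 4200 + 1000 = 5200.

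**2. Tests by site at T0, from the Table 5 caption.**

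| Test | Intervention site | Control site |
|---|---|---|
| Antibody assay, PCR, CAA assays | yes | yes |
| Microscopy | yes | no (Table 4: no site limit) |
| POC-CCA, laboratory | yes | yes |
| POC-CCA, on-site | yes | no |

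The location of the panel also varies. The analysis section points to Table 5, the T0 visit description to Table 4 and the Fig. 3 caption to Table 3.

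**3. How much microscopy could matter.** Only the prevalence p = 0.25 comes from the plan (Sample size and statistical analysis). The assumptions are:
- POC-CCA sensitivity 0.85 and specificity 0.90;
- a rest-of-panel with sensitivity R = 0.60 to 0.95 and specificity C = 0.90 to 0.98;
- microscopy sensitivity M = 0.30 to 0.60 and specificity 1;
- any positive test makes a woman reference-positive;
- tests are independent given infection status.

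Panel sensitivity S is R without microscopy and 1 − (1 − R)(1 − M) with it.

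Apparent specificity = [p(1 − S)(0.15) + (1 − p)C(0.90)] / [p(1 − S) + (1 − p)C]

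Worked case, R = 0.80, C = 0.98, M = 0.60:
- without microscopy: (0.05 × 0.15 + 0.735 × 0.90)/(0.05 + 0.735) = 0.669/0.785 = 85.2%;
- with microscopy, S = 0.92: (0.02 × 0.15 + 0.735 × 0.90)/(0.02 + 0.735) = 0.6645/0.755 = 88.0%.

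| R / C | M | Without | With | Gap (points) |
|---|---|---|---|---|
| 0.95 / 0.98 | 0.30 | 88.7% | 89.1% | 0.4 |
| 0.80 / 0.98 | 0.60 | 85.2% | 88.0% | 2.8 |
| 0.80 / 0.90 | 0.60 | 84.8% | 87.8% | 3.0 |
| 0.60 / 0.98 | 0.60 | 81.0% | 86.1% | 5.1 |

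Over the cases run, apparent sensitivity moves by 0.1 to 2.0 points. At an assumed prevalence of 0.50, twice the plan's, the specificity gap runs from 1.1 to 11.2 points.

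**4. Sampling error.** For specificity 0.90 and prevalence 0.25:
- 1000 women, 750 uninfected: 1.96 × √(0.9 × 0.1/750) = 2.1 points;
- an assumed 500 women at one site, 375 uninfected: 1.96 × √(0.9 × 0.1/375) = 3.0 points.

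**5. What a common panel without microscopy costs.** Take a simpler model: 500 women per site, 25% infected, POC-CCA 80%/90%, and a panel without microscopy that misses 10% or 30% of infections (12.5 or 37.5 women per site). Suppose also that the panel with microscopy is perfect.

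- Common panel without microscopy at both sites: (337.5 + 0.2 × 12.5)/387.5 = 340/387.5 = 87.7%, and (337.5 + 0.2 × 37.5)/412.5 = 345/412.5 = 83.6%. The bias against 90% is 2.3 to 6.4 points.
- Mixed pooling as written: (337.5 + 340)/(375 + 387.5) = 677.5/762.5 = 88.9%, and (337.5 + 345)/(375 + 412.5) = 682.5/787.5 = 86.7%. The bias is 1.1 to 3.3 points.

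Under this model the uniform panel gives a consistent definition but a larger downward bias in specificity.

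**The case against.** **The index test.** A reader might infer that the index test itself differs by site, so that the pooled results describe neither laboratory nor routine-care accuracy. The documents do not support that. The Table 5 caption provides a laboratory POC-CCA for every T0 sample, so a uniform index test is available for all 1000. What stands is narrower: the analysis text does not separate the two readings, and only the on-site one speaks directly to routine care.

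**Microscopy at one site is not settled.** Only the Table 5 caption states the restriction, and the tables themselves are not shown. Stool from 1000 women could serve PCR, so stool collection alone does not show that microscopy is done at both sites. But the unqualified microscopy statement in the Table 4 caption does not agree with the Table 5 caption. This calls for reconciliation; it does not prove a design flaw.

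**The combination rule is unseen.** Reference status shifts by site only if microscopy alone can change it. The rule may be in the full protocol or the SAP, so its absence is not counted here. The article also does not exclude reporting by site.

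**Size.** It is tempting to read 1 to 3 points as the bias of the planned analysis. That assumes a perfect reference wherever microscopy is done. The gap between sites reflects only what microscopy recovers. If it recovers half of the missed infections, the gap in the simple model falls from 2.3 to 1.1 points (338.75/381.25 = 88.9% against 87.7%) or from 6.4 to 3.0 points (341.25/393.75 = 86.7% against 83.6%). If PCR and the CAA assays find nearly all infections, the effect is negligible.

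**Conclusion.** The point holds in a limited form. As written, the plan sets 1000 women from two sites against one combined panel, while its own Table 5 gives the two sites different panels and Table 4 does not agree. If microscopy can alter reference status, the reference standard differs by site.

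At the plan's prevalence of 25% the effect on apparent specificity runs from negligible (0.4 points) to about 5 points, against a sampling half-width of about 2 points. That range rests on assumed test accuracies, an any-positive rule and conditional independence, none of which the article states. The effect on apparent sensitivity is smaller, at most 2 points in the cases examined.

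The matter concerns a secondary endpoint at non-randomized sites and touches neither primary endpoint. It is worth correcting because the change is one of wording and reporting.

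**What to change.** 1. Reconcile Tables 4 and 5 on where microscopy is done, and make the text point to one table for the reference panel. If microscopy is in fact done at both sites, correct the Table 5 caption; the site difference in the reference then disappears.
2. If the restriction stands, name the laboratory POC-CCA as the index test for the 1000 samples and report sensitivity and specificity by site.
3. Pool the sites only against a panel made of tests run at both. State that this panel is less sensitive and may bias apparent specificity downward.
4. At the intervention site, also report results with microscopy in the reference.
5. Report the on-site POC-CCA at the intervention site separately, as the estimate of routine-care accuracy.

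A latent class model is optional and not part of the required change.

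The cost is precision and wording, with no extra testing. Single-site specificity would carry a half-width of about 3 points (assumed 500 women, 25% prevalence), against about 2 points for 1000. For a sensitivity of 0.85 the half-widths are 1.96 × √(0.85 × 0.15/125) = 6.3 and 1.96 × √(0.85 × 0.15/250) = 4.4 points.

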### Sample size and statistical analysis

The sample size was calculated in relation to the primary child outcome proportion showing stunted growth at 2 years of age, for which a larger sample size is assumed to be necessary than for the maternal outcome (Hb, 2 years after delivery).

The prevalence of stunting in Madagascar is estimated to be 40% of children under 2 years of age [26]. For our sample size estimate, it was conservatively assumed that:
Twenty per cent of all children at the age of 2 years are stunted (height-for-age *z*-score < − 2)The intervention can reduce the proportion of stunted children by 50% in infected individuals, i.e. to observe that 10% of all children at the age of 2 years are stunted in the intervention arm.

In order to estimate the appropriate number of infected individuals at 9 months of age, sample sizes with power values of 80% and 90% were subsequently calculated using the OpenEpi tool [27]. For a power of 80%, at least 394 infected individuals at 9 months of age would be required and for a power of 90% 526 individuals. The design effect was assumed to be 1.9 by which the initial sample size needs to be multiplied to account for the clustered design of the study. This leads to a sample size of 749 for 80% power and 1000 for 90% power.

With an annual loss to follow-up of 10% from a visit to visit and an infant mortality rate of 4%, 86% of all mother-infant tandems are expected to present for the 9-month visit. For the 2 years visit, a loss to follow-up of around 10% between 9 months and 2 years is assumed, so that around 0.86 × 0.9 = 77.4% of all mother-infant tandems are expected to present for the 2-year visit. To correct for loss to follow-up, we use the factor 1/0.774 = 1.3. Since our analyses only focus on women infected with schistosomiasis, the number of women to be recruited needs adjusting, considering that the expected prevalence of 0.25 results in an additional inflation factor of 4 leading to an inflation factor of 1.3 × 4 = 5.2.

We hence planned to enrol 4200 eligible pregnant women in the 40 randomized cluster of the trial ensuring a power between 80 and 90% and an additional 1000 participants for the cross-sectional sub-study in the non-randomized sites. Based on the 40 randomized clusters identified for this study, an average of 105 women per cluster is needed to be recruited per cluster.

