### Analysis for the primary outcomes

For the main child endpoint, the proportion of stunted children (height-for-age *z*-value < − 2) at 2 years will be compared between the intervention and control arm using the chi-square tests and *t*-tests. Reference standards from Madagascar as reported by the WHO [28] will be considered in the analysis. For the maternal main endpoint, the difference in Hb 2 years after delivery will be compared between the intervention and control arms using the *t*-tests. For all analyses, a significance level of alpha *=* 0.05 is assumed. Additional analyses will be performed using mixed-effects logistic and linear regression models to account for the between-cluster variation as a random effect. Secondary and other outcomes that are normally distributed will be analysed in the same way.

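### The protocol contradicts itself on the primary analysis population, and its stated 80–90% power holds only if the infected quarter is the group analysed

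*Protocol article*

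**What the plan says.** The section on sample size and statistical analysis starts from "Twenty per cent of all children at the age of 2 years are stunted" and assumes that the intervention halves the proportion stunted "in infected individuals, i.e. to observe that 10% of all children at the age of 2 years are stunted in the intervention arm". One sentence thus gives the effect both for the infected and for all children. It derives 394 infected individuals for 80% power and 526 for 90%, describing them as infected at 9 months of age. It multiplies by a design effect of 1.9 (749 and 1000), by 1.3 for losses, and by 4 for a prevalence of 0.25. The reason given for the last factor is "Since our analyses only focus on women infected with schistosomiasis, the number of women to be recruited needs adjusting". The planned 4200 women in 40 clusters are described as "ensuring a power between 80 and 90" per cent.

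The Outcomes section, and the summary of units of analysis under Trial design and location, define the child endpoint as the proportion of children stunted at 2 years. The section on analysis for the primary outcomes begins "For the main child endpoint, the proportion of stunted children" and compares that proportion between arms. None of these three places limits the comparison to infected women or infected children.

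**The concern.** The power statement and the primary comparison appear to belong to different populations. In addition, a halving among infected individuals equals 10% of all children only if every child is infected, yet the plan puts prevalence at a quarter.

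The results are meant to inform national guidance. If the unrestricted comparison is the primary one, any effect is diluted by the uninfected majority, and a null result could be taken as evidence against the strategy when the comparison had too little power. If the infected-only comparison is the primary one, the document does not say whose infection counts, at which visit, or by which test. Settling that after the data are seen would weaken a positive result.

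**Working it through.** **Inputs, all from the sample size section unless noted.** Control rate 20%; 50% reduction in the infected; design effect 1.9; retention to 2 years 77.4%; prevalence 0.25; 4200 women in 40 clusters, 1:1 (Randomization section). Alpha is 0.05 (analysis section). Sidedness is not stated; two-sided is assumed, and it reproduces the plan's figures.

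**1. The plan's own figures.** With n per arm = (1.96 + z_power)² × [0.20×0.80 + 0.10×0.90] / 0.10²:
- 80% power: 196.2, rounded up to 197, times 2 = 394.
- 90% power: 262.7, rounded up to 263, times 2 = 526.

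Both match. Then 394 × 1.9 = 748.6 and 526 × 1.9 = 999.4. Multiplying 749 and 1000 by 5.2 gives 3895 and 5200 women, and 4200 lies between them.

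**2. Power if only the infected quarter is analysed.** 4200 × 0.774 × 0.25 = 813 tandems. The effective number per arm is 813 / 1.9 / 2 = 213.9. Power = Φ{[d − 1.96·√(2p̄(1−p̄)/n)] / √([p₁(1−p₁)+p₂(1−p₂)]/n)}, with d = 0.10 and p̄ = 0.15: Φ{(0.10 − 1.96×0.03453) / 0.03419} = 82.8%. This is where the 80–90% statement comes from.

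**3. The all-children rate.** If infected and uninfected children share the 20% rate, the intervention arm has 0.75×20% + 0.25×10% = 17.5%.

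**4. Power without restriction, equal risk.** 4200 × 0.774 = 3251 children. The effective number per arm is 3251 / 1.9 / 2 = 855.5. With d = 0.025: Φ{(0.025 − 1.96×0.01887) / 0.01886} = 26.3%. For 80% or 90% power the same formula needs 7652 or 10,242 children before clustering, 14,539 or 19,460 after × 1.9, and about 18,800 or 25,100 women enrolled after dividing by 0.774.

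**5. Design effect.** The document does not say which cluster size 1.9 refers to. If it was meant for the infected, 813 / 40 = 20.3 per cluster, the implied intracluster correlation is 0.9 / 19.3 = 0.0466. At 3251 / 40 = 81.3 children per cluster the design effect becomes 1 + 80.3 × 0.0466 = 4.74, and equal-risk power is 13.1%. If 1.9 was meant for all 105 enrolled per cluster, the design effect is 1 + 80.3 × 0.9/104 = 1.69 and power is 28.9%.

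**6. Higher stunting risk in the infected (assumed, not in the document).** For overall control rate B and risk ratio R, the uninfected rate is p₀ = B / (0.75 + 0.25R), and the intervention arm has 0.75p₀ + 0.5×0.25×R×p₀. Power for all children:

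| Control rate | R | Intervention rate | Design effect 1.9 | Design effect 4.74 |
|---|---|---|---|---|
| 20% | 1 | 17.5% | 26% | 13% |
| 20% | 1.5 | 16.7% | 43% | 20% |
| 20% | 2 | 16.0% | 58% | 27% |
| 20% | 3 | 15.0% | 78% | 41% |
| 40% | 1 | 35.0% | 57% | 27% |
| 40% | 1.5 | 33.3% | 82% | 44% |
| 40% | 2 | 32.0% | 93% | 59% |

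The 40% rows use the national figure that the section cites before choosing 20% as conservative. At the lower design effect of 1.69, the 20% baseline passes 80% only at R = 3 (82%).

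**7. The literal reading.** If 20% v 10% is meant for all children, power with 855.5 effective per arm exceeds 99.9%. The 80–90% statement does not fit that reading either.

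**The case against.** The sample size section does say that the analyses concern infected women, and it is the only place that names an analysis population. The analysis section refers to stunted children without saying all. Table 5 plans laboratory testing of T0 samples from all women at all sites, so an infected-only analysis is feasible, and on that reading the stated power is right. The document is a condensed article, and populations are often defined in an analysis plan that is not shown. The 26% figure also needs equal stunting risk in infected and uninfected children, which sits badly with the trial's rationale that infection impairs growth.

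Much of this stands. A reader might infer that the trial has 26% power rather than 80–90%. The documents do not support that as a flat statement, because it picks one of two conflicting readings and one set of unstated inputs. Nor can 17.5% simply be written in as the correct all-children rate. A reader might also infer that the maternal haemoglobin comparison is underpowered by the same dilution. The protocol gives no effect size or standard deviation for haemoglobin and assumes that it needs the smaller sample, so nothing can be calculated.

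The contradiction itself is not answered. The restriction appears only as the reason for an inflation factor and is missing where the endpoint and analysis are defined. It also shifts from infection at 9 months of age to infection of the woman. An unseen analysis plan may supply missing detail, but it does not make these statements agree.

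**Conclusion.** The point holds as a contradiction about who is in the primary comparison, with a power claim that is true under only one reading. Restricted to the infected quarter, power is about 83%, as claimed.

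Unrestricted, with the plan's 20% baseline and design effect of 1.9, power runs from 26% (equal risk) to 78% (assumed threefold risk), and a design effect rescaled to 81 children per cluster lowers every figure. At design effect 1.9, the unrestricted comparison passes 80% in the cases tested only when the cited 40% baseline is combined with an assumed higher risk in the infected. A shortfall is therefore likely if all children are primary, but its size depends on inputs that the document does not give.

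Separately, the equation of a halving in the infected with 10% of all children is wrong at a prevalence of 0.25, whatever the risk ratio: the uninfected three quarters keep their stunting rate, so the overall rate is not halved.

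**What to change.** 1. Align the Outcomes, sample size and primary analysis sections on one named primary population. If it is the infected, define infection by a measure taken before treatment and obtained in the same way in both arms. The central-laboratory testing of T0 samples, already planned for all women at all sites, meets this; the protocol should name the assay. Status at 9 months is less suitable, because in the intervention arm it follows maternal treatment and may be altered by it. Reconcile the 9-month and maternal bases now used side by side in the sample size section.
2. Attach the 80–90% statement to the infected-only comparison. Report the all-children comparison as the strategy-level result, with its own power shown as a range and the baseline, risk ratio and design effect labelled. If all children stay primary, replace the 80–90% statement with that range.
3. Change the 10% of all children to 10% of infected children. Give any all-children rate, such as 17.5% under equal risk, as a labelled assumption.

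Mean height-for-age z-score could be added as a supportive endpoint, but this is optional. The cost is wording and a restated power figure, with no extra participants or samples. The choice of population should be fixed before outcome data are compared by arm.
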